### DATA ANALYSIS

Descriptive statistics will be reported to describe the study population. Proportions will be reported for categorical data, the mean and standard deviation will be reported for continuous normal data while the median and Inter-quartile range [IQR] will be reported for non-normal data. Proportions in each study arm will be compared for the secondary outcome.

Data will be analysed using STATA analytical package version 13,while presentation will be inform of charts and graphs for descriptive statistics while tables will be used for the presentation of inferential statistics. All statistical tests will be performed at 5% level of significance (p value<0.05) while odds ratios and corresponding 95% confidence intervals will be reported for regression analysis.

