**Analysis plan**: Levels of haemoglobin and haematocrit of newborn infants following umbilical cord milking will be compared to those of newborns who undergo delayed cord clamping using unpaired students T- test and a P value <0.05 for significance. Prevalence will be compared using proportions and chi squared test of independence. Measurements of excess risk will be estimated using relative risk at 95%confidence interval that excludes the null value will be considered significant. Intention to treat analysis will be used.

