# SAMPLE SIZE:

Using the formula for sample size calculation (Chow S, Shao J, Wang H. 2008).

$$n=\frac{r+1}{r}\frac{{{SD}^{2}\left( Z_{\beta}+Z_{\alpha/2} \right)}^{2}}{d^{2}}$$

Where:

SD **=** standard deviation from a previously published study=2

d=expected mean difference between the groups

r=ratio for the groups= 1:1

$Z_{\beta}$**=**standard normal variation for level of power=80% power is 0.84

Z$\alpha/2$= standard normal variation for level of significance= 1.96

In a similar study done by Katheria AC(24), using the mean value for haemoglobin for UCM and DCC, we get our sample size as follows:

$$n=\frac{1+1}{1}\frac{{2^{2}\left( 0.84+1.96 \right)}^{2}}{{0.7}^{2}}$$

n= 128 per arm

To account for attrition bias an additional 10 percent will be added to the total sample size.

Therefore a total sample size of 280 will be required for the study.

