**Table 3: Association between delayed cord clamping versus umbilical cord milking and maternal/neonatal complications**

|  | | DCC | UCM | RR | P value |
| --- | --- | --- | --- | --- | --- |
| Maternal | Post partum haemorrhage  Need for blood transfusion |  |  |  |  |
| Fetal | Polycythemia |  |  |  |  |
|  | Neonatal polycythemia |  |  |  |  |
|  | Neonatal jaundice |  |  |  |  |
|  | Need for blood transfusion |  |  |  |  |
|  | Need for phototherapy |  |  |  |  |

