**Part Ill: Index Admission**

1. Date of Admission ……/……./…….
2. Time of admission ……………….
3. Referral status

Referred from other facility □

Self referred □

Booked for delivery at KNH □

1. Gestational age at delivery (in completed weeks) ……../40
2. Gestational age calculated by Dates □ Quickening □

Ultrasound □ Fundal Height □

First clinic visit estimate □

1. Maternal Haemoglobin levels at admission ……………..
2. Maternal PCV at admission ………….
3. Maternal use of drugs for medical condition yes no
4. State which illness medication is used for in Q22 above.

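### The primary haemoglobin and haematocrit comparison is a valid but unadjusted t-test that gives up precision, and the plan does not say how its undefined odds-ratio regression relates to the relative risks promised elsewhere

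*Protocol*

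**What the plan says.** **Continuous outcomes.** The analysis plan in the Abstract compares haemoglobin and haematocrit between arms "using unpaired students T- test and a P value <0.05 for significance". No covariate is named. The Data Analysis section names no test for these outcomes and refers only to means with SDs, or medians with interquartile ranges. Dummy Table 4 has columns for the mean and SD in each arm and a p value, with no column for a difference or its confidence interval.

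**Binary outcomes.** The Abstract says: "Prevalence will be compared using proportions and chi squared test of independence". It adds: "Measurements of excess risk will be estimated using relative risk at 95%confidence interval". Dummy Table 3, which covers jaundice, polycythaemia and postpartum haemorrhage, has the columns "DCC | UCM | RR | P value". The Data Analysis section does not mention relative risk. It says that "odds ratios and corresponding 95% confidence intervals will be reported for regression analysis", and gives no outcome, covariates or model for that regression.

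**Covariates and design.** Eligibility runs from 28 to <37 weeks. The Randomization section describes blocks but no strata. The data collection tool (Appendix III, index admission part) records gestational age at delivery, how it was dated, and "Maternal Haemoglobin levels at admission". Its only column for mode of delivery is in the table of previous births.

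**The concern.** The protocol itself treats these blood values as dependent on gestation: its operational definition of polycythaemia is relative to normal for gestational age. It also cites higher initial haemoglobin with milking in caesarean births, and its flow diagram separates vaginal from caesarean delivery. A t-test across nine weeks of gestation leaves that variation in the error term. With no stratification stated in the Randomization section, neither the design nor the analysis deals with a chance imbalance in gestational age.

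For the binary outcomes, two effect measures are promised and nothing says which is the trial's estimate. Jaundice and polycythaemia stand under the primary objectives in the Study objectives section, so the choice matters. For a common event the two measures can look very different from the same data.

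Mode of delivery of the index birth is needed for dummy Table 1 and for the flow diagram. It is also needed to classify postpartum haemorrhage, because the operational definition uses a different volume for each route. The data collection tool has no field for it. The screening form in Appendix II asks about vertex or caesarean birth in a single item, which does not record which one occurred.

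**Working it through.** **1. The plan's own figure.** The inputs, all from the Sample Size section, are SD 2, difference 0.7, Zβ 0.84, and the "standard normal variation for level of significance= 1.96".

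n per arm = 2 × SD² × (Zβ + Zα/2)² / d² = 2 × 4 × (2.80)² / 0.49 = 62.72 / 0.49 = 128.

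This reproduces the stated 128 (unrounded z values give 129). Adding 10% to 256 gives 281.6, against the stated 280, or 140 per arm. Losing 10% of 140 leaves 126 per arm. The SD of 2 is a total SD, so the calculation is for an unadjusted comparison, and the t-test fits it.

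**2. Effect of adjustment.** If baseline covariates explain a share R² of haemoglobin variance, the residual SD is 2 × √(1 − R²). Power ≈ Φ(0.7 / [SD × √(2/n)] − 1.96). With n = 126, √(2/126) = 0.126.

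| R² (assumed) | Residual SD | Power at 126 per arm | n per arm for 80% power |
| --- | --- | --- | --- |
| 0 | 2.000 | 79.3% | 129 |
| 0.05 | 1.949 | 81.3% | 122 |
| 0.10 | 1.897 | 83.4% | 116 |
| 0.20 | 1.789 | 87.4% | 103 |

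Example for R² = 0.10: 0.7 / (1.897 × 0.126) = 2.93; 2.93 − 1.96 = 0.97; Φ(0.97) ≈ 0.83. A calculation based on the t distribution gives values 0.2 to 0.3 points lower. The protocol gives no R², so the table shows a range and is not a forecast.

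**3. Odds ratio against relative risk.** With control risk p0 and p1 = RR × p0, OR = [p1/(1 − p1)] / [p0/(1 − p0)]. For a true RR of 1.3:

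- p0 = 10%: (0.13/0.87) / (0.10/0.90) = 1.34
- p0 = 30%: (0.39/0.61) / (0.30/0.70) = 1.49
- p0 = 50%: (0.65/0.35) / (0.50/0.50) = 1.86

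The protocol states no expected rate of jaundice, so all three control risks are assumptions.

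**4. The form against its uses.** Dummy Table 1 lists mode of delivery in three categories, the flow diagram counts vaginal and caesarean births, and the haemorrhage definition depends on route. None of the five parts of the data collection tool records the route of the index birth.

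**The case against.** The strongest reply is that the t-test is not an error. Under 1:1 randomisation it is valid, and it is the test for which the sample was sized. A reader might infer from the wide gestational range that the comparison is biased or underpowered. The documents do not support that: 128 per arm reproduces, and 126 per arm is the full-attrition case. At the protocol's own retention goal of at least 95%, about 133 per arm, unadjusted power is about 81%; at 140 it is 83.4%. The gain from adjustment rests on an assumed R² and may be as small as 2 points. The form also allows dating by quickening, fundal height or first-visit estimate, and such imprecise dating would tend to lower R². Covariates are often left to the statistical analysis plan. All of this stands, and it makes the point one of efficiency. It does not remove the reason to use a baseline factor that is already recorded.

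A reader might also infer that the plan will overstate effects on jaundice. That does not follow. Table 3 assigns jaundice a relative risk, the odds ratios are confined to a regression, and the two could coexist. An odds ratio exaggerates only if it is read as a relative risk and the event is common, and no rate is given. What remains is that the regression is undefined and its relation to the relative risks is not stated.

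On mode of delivery, the protocol clearly intends to capture it, since a table and the flow diagram call for it. The gap is in the form.

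**Conclusion.** The point holds as an improvement in precision together with an unresolved choice of effect measure. The planned t-test is valid and delivers close to its planned power. Adjustment would add about 2, 4 or 8 percentage points at 126 per arm if baseline factors explain 5%, 10% or 20% of haemoglobin variance. It would also give some protection against chance imbalance, and it needs no extra participants.

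For the binary outcomes, the Abstract and Table 3 agree on relative risk, and the Data Analysis section adds odds ratios from a model that it does not describe. The practical consequence is slight if the outcome is uncommon and clear if it is common; the protocol does not allow a choice between the two. The missing field for mode of the index delivery is certain on the form as shown.

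These changes should be made, but none of them calls the validity of the trial into question.

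**What to change.** 1. **Primary analysis.** Use linear regression of 24-hour haemoglobin, and likewise haematocrit, on arm, gestational age dated before birth (last menstrual period or ultrasound, not the Ballard score done at 24 hours) and mode of delivery. Maternal haemoglobin is optional. Report the adjusted mean difference with its 95% CI, add that column to dummy Table 4, and keep the t-test as a sensitivity analysis.
2. **Binary outcomes.** State that relative risk, with the risk difference, is the effect measure for jaundice, polycythaemia, anaemia and postpartum haemorrhage. Anaemia has no row in Table 3 and needs one. Delete the odds-ratio sentence, or limit it to a secondary model whose outcome and covariates are named.
3. **Data form.** Add a field for the mode of the index delivery. Randomisation takes place in second stage or at induction of anaesthesia, so recording the route intended at that time as well would keep the covariate a baseline one.

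The cost is minor analysis wording, small edits to two dummy tables and one item on the form. Sample size and trial procedures do not change.

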# ETHICAL CONSIDERATIONS

### Ethical Review

This protocol and the template informed consent form found in appendix, and any subsequent modifications to this form, will be reviewed and approved by the Kenyatta National Hospital/University of Nairobi Ethics Research Committee prior to initiation of the study, with respect to scientific content and compliance with applicable research and human subjects regulations.

This protocol, the informed consent form, and any other requested documents, as well as any subsequent modifications, will be reviewed and approved by the Ethical Review Committee.

Safety and progress reports will be submitted to the KNH-UoN ERC, after study completion or in case of study termination or occurrences of any adverse events. The reports will include the total participants enrolled in the study, the number of participants that completed the study, all changes in the research activity, and all other problems that were not anticipated that involves risks to human subject or others. Finally, all open DSMB reports will be provided to the KNH-UoN ERC.

### Informed consent

We will obtain a written informed consent from participants or from the parents/guardians of participants who in one way or the other cannot consent for themselves. Adequate explanation and counseling will be done before consenting. Participant’s partner will be informed about the study. If the participant requests the partner’s presence or advice before consenting, they will be granted if the partner is within the Hospital. They will then append their signature as a witness as provided for in the consent form. However the participant’s approval will be considered as tacit approval from the partner, unless otherwise specified.

The informed consent form describes the purpose of the study, the procedures to be carried out, the risks and benefits in accordance with applicable regulations. The consent form will be translated into Swahili for ease of understanding.

Literate participants will append their signatures at the provided space in the consent form. Non-literate participants will document their approval by marking the form using their thumbprint, in the presence of a literate third party witness. Any other local ERC requirements for obtaining informed consent from non-literate persons will be followed. Participants or their parents/ guardians will be provided a copy of their informed consent forms and this fact will be documented in the participant’s record

### Risks

Risks will be anticipated and addressed accordingly. Side effects of delayed cord clamping and umbilical cord milking are rare. In case the neonate requires immediate resuscitation, this will be attended to.

We will ensure the participants privacy and confidentiality is maintained at all times. However it is possible that others will know of the participant’s involvement in the study, although we think there's no stigma related to this, and any potential harm will be alleviated.

### Benefits

If umbilical cord milking is found to be more beneficial for the premature, they will gain by receiving the best obstetric practice especially in scenarios where time is of importance and neonatal resuscitation is required. The findings will benefit the participants in case the positive findings are implemented at a later date. The information learnt from this study may in future help the participants and others.

### Confidentiality

Information collected to be handled with Belmont’s principles of confidentiality (Respect for persons, Beneficence and Justice). Each participant will be allocated a unique study identification number for confidentiality. The coded number will identify all reports, data collected and other administrative forms. All the information on the participants and the study as a whole will be stored and secured at the study site and stored in locked file cabinets only accessible by study staff. All databases will be secured with password-protected access systems. The study information of the participants will not release without the written permission of the participant, except for monitoring by the DMSB, or KNH-UoN-ERC.

### Study discontinuation

The study's goal is to achieve ≥ 95% participant retention. So we will make every reasonable effort to retain any enrolled study participant to completion of the study. Participants are at will to withdraw from the study if they are unwilling or unable to comply with the required study procedures. In order to protect participants’ safety, the Principal investigator may withdraw study participants from the study.

A final evaluation will be completed for the study participants who withdraw from the study before completion. And the reasons for the withdrawal will be recorded in the participant’s records.

Finally the study may be discontinued at any time by the KNH-UoN-ERC.

### Training

The research team involved will undertake Good Clinical Practice (GCP) training and certification. Once the study has been approved, it will be registered with the clinical trial registry and clinicaltrial.gov.

Consolidated standards of reporting trials (CONSORT) will be used to facilitate complete and transparent reporting of the trial.

Training of research assistants will take place over the duration of one week; initially they will observe the process of obtaining informed consent and filling of the questionnaires. Thereafter they will work under supervision until the principal investigator is satisfied. The principal investigator will constantly review the questionnaires for completion. Research assistants and midwives will undergo training prior to commencement of the study via video tutorials and clinical teachings. Each will undertake good clinical practice certification once the study is approved.

# STUDY LIMITATIONS

The study lacks addition of another control arm to undergo immediate cord clamping. Given the recent evidence on benefits of placental transfusion and adverse effects of ICC there was not enough clinical equipoise to have assigned an ICC arm.

The time period of follow-up is focused on short term outcomes due to timeline limitations, it would be more enriching to have long term outcomes. This cohort can therefore be followed up in another study evaluating the long term outcomes.

The study is not primarily designed to assess possible adverse effects of placental transfusion, however previous studies have disproved a correlation between placental transfusion interventions and PPH, neonatal polycythemia and hyperbilirubinaemia.

It will not be possible to measure the amount of blood actually transfused from the placenta into the newborn child.

# DISSEMINATION OF RESEARCH FINDINGS

All participants in the research will be given a report of the findings, and will be encouraged to comment on them.

As well as the above, dissemination of the results will take place by three methods:

- Production of a report that will be sent to the department of obstetrics and gynaecology as well as the department of paediatrics.
- Publishing papers in specialist and general, national and international journals.
- Presentation of papers at both national and international conferences.

# STUDY TIMELINE

|  |  | | |  |  | | |  | |  | |  |  |
| --- | --- | --- | --- | --- | --- | --- | --- | --- | --- | --- | --- | --- | --- |
|  | **2017** | | **2018** | | | | | | | | | |  |
|  | **August-November** | **December** | **January-February** | | | **March-May** | **June** | | **July** | | **August-** | |  |
| Proposal Development |  |  |  | | |  |  | |  | |  | |  |
| Proposal Presentation |  |  |  | | |  |  | |  | |  | |  |
| Ethics Committee Review |  |  |  | | |  |  | |  | |  | |  |
| Data Collection |  |  |  | | |  |  | |  | |  | |  |
| Data Analysis |  |  |  | | |  |  | |  | |  | |  |
| Results Presentation |  |  |  | | |  |  | |  | |  | |  |
| Publication |  |  |  | | |  |  | |  | |  | |  |

# BUDGET

|  | **Item** | **Amount (Kes)** |
| --- | --- | --- |
| Proposal  Development | Printing: questionnaires | 10,000 |
|  | Opaque envelopes | 2,500 |
|  | Proposal copies | 6,000 |
|  | KNH-UoN ERC | 2,000 |
| Data Collection | Training research assistants | 3,000 |
|  | Research Assistants x 2 pax | 90,000 |
|  | Stationary | 2,500 |
|  | Laboratory costs | 180,000 |
|  | Internet | 15,000 |
|  | Airtime | 5,000 |
|  | Transport/Meetings | 5,000 |
| Equipment | Hypodermic needles, cotton swabs, spirit, EDTA bottles, clean gloves, | 50,000 |
|  | External hard drive |  |
|  |  | 10,000 |
| Data Analysis | Statistician | 50,000 |
| Thesis write up | Printing drafts | 5,000 |
|  | Printing thesis | 6,000 |
|  | Contingency | 30,000 |
|  | TOTAL | **472,000** |

# Dummy tables

**Table 1: Maternal baseline characteristics**

| Characteristic | Category | n (%) / mean (SD deviation)  DCC | n(%)/ mean (SD deviation)  UCM | P value |
| --- | --- | --- | --- | --- |
| Socio demographics | | |  |  |
| Age | 18-25  26-35  36-50  >50 |  |  |  |
| Obstetric History | | |  |  |
| Parity | 0  1  2  3  4  5 |  |  |  |
| ANC attendance | Yes  No |  |  |  |
| Facility attended | KNH  Other facility |  |  |  |
| Number of visits | 1  2-4  >4 |  |  |  |
| Gestational age at first visit | |  |  |  |
| Hb(g/dl) at 1^st^ visit | |  |  |  |
| Repeat Hb( If available) | |  |  |  |
| Blood group | A+  B+  AB+  O+  A-  B-  AB-  O- |  |  |  |
| VDRL | Positive  Negative  Unknown |  |  |  |
| HIV | Positive  Negative  Unknown |  |  |  |
| Medications | Magnesium-sulphate  Steroids  Antihypertensive  Narcotics |  |  |  |
| Mode of delivery | Spontaneous vertex delivery  Caesarean section  Assisted vaginal delivery |  |  |  |

**Table 2: Infant baseline characteristics**

| Variable |  | DCC | UCM | P value |
| --- | --- | --- | --- | --- |
| Sex  Gestational age  APGAR score  Birth weight  Birth length  Head circumference  Need for neonatal resuscitation  NICU admission | Male  Female  At 1 min  At 5 min |  |  |  |

**Table 3: Association between delayed cord clamping versus umbilical cord milking and maternal/neonatal complications**

|  | | DCC | UCM | RR | P value |
| --- | --- | --- | --- | --- | --- |
| Maternal | Post partum haemorrhage  Need for blood transfusion |  |  |  |  |
| Fetal | Polycythemia |  |  |  |  |
|  | Neonatal polycythemia |  |  |  |  |
|  | Neonatal jaundice |  |  |  |  |
|  | Need for blood transfusion |  |  |  |  |
|  | Need for phototherapy |  |  |  |  |

**Table 4: neonatal haematological outcomes**

|  |  | DCC | UCM | P value |
| --- | --- | --- | --- | --- |
|  |  | Mean(SD) | Mean(SD) |  |
| Neonatal Hb(g/dl) |  |  |  |  |
| Neonatal Hct (%) |  |  |  |  |
| Serum bilirubin(mg/dl) |  |  |  |  |

# APPENDICES

## APPENDIX II: INCLUSION AND EXCLUSION SCREENING ENROLMENT FORM

**Study Title:** **THE EFFECT OF UMBILICAL CORD MILKING VERSUS DELAYED CORD CLAMPING ON SELECTED HAEMATOLOGICAL AND CLINICAL PARAMETERS IN PRETERM NEONATES AT KENYATTA NATIONAL HOSPITAL**

Date: (date/month/year):

Code Number of the Mother-Baby pair: ________________________

Subject Initials: _____________

*Inclusion Criteria: Answers MUST be ‘yes’ for both questions*

1. Gestation between 28 to <37 weeks at time of presentation
2. Live Neonate born via spontaneous vertex delivery or caesarean delivery.
3. Informed consent must be provided.

*Exclusion criteria*: *If any answer is ‘Yes’ exclude from enrolment*

1. Multiple gestations.
2. Placental separation before delivery.
3. Tight nuchal cord necessitating early cutting.
4. Need for neonatal resuscitation.
5. Major congenital abnormalities (e.g. neural tube defects).
6. Red cell isoimmunisation.
7. Positive serology for Human immunodeficiency virus Venereal disease research laboratory.
8. Declined consent.

## APPENDIX III: DATA COLLECTION TOOL

**Study Title:** **THE EFFECT OF UMBILICAL CORD MILKING VERSUS DELAYED CORD CLAMPING ON SELECTED HAEMATOLOGICAL AND CLINICAL PARAMETERS IN PRETERM NEONATES AT KENYATTA NATIONAL HOSPITAL**

**BASELINE QUESTIONNAIRE**

**Part I: Socio demographics**

**Indicate all times using the 24 hour clock, and dates in this format date/month/year.**

DATE__________

Code number of mother-infant pair:_________ Randomization arm: ___

Date of Signed Informed Consent: ____/______/_____

Copy given to patient: Yes / No

1. Age of mother (years) ……………………………….
2. Marital Status

Single □ Widowed □

Married □ Separated □

Divorced □

1. Level of Education

Primary □ Secondary □ Tertiary □

1. Employment status

Self employed □ Salaried employment □ Unemployed □

